### Statistical analysis

The statistical analysis will be carried out using the IBM SPSS Statistics 26 software. Descriptive statistics will be used to describe the study population and will be summarised per group based on the number of observations, means and standard deviations. The primary and secondary outcome variables (VAS, NDI, CROM, PPT and GPE) will be analysed by intention to treat and by using linear mixed models with repeated measures. The linear mixed model requires the residuals to be normally distributed. The Shapiro–Wilk test will be applied to test the normality. In case of a non-normal distribution of the residuals, an appropriate non-parametric test will be conducted. Multiple post-hoc comparisons will be conducted through Bonferroni’s contrast for parametric distributions. All tests will be two sided, and the level of significance is set to 0.05. The missing data in this study will be handled with a mean imputation or mixed modelling approach.

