**Methods:**

We will conduct a prospective randomised controlled trial including 150 patients with WRNP. These patients will be randomly assigned to one of three groups: (i) home exercise (TE), (ii) home exercise plus Occiflex therapy and (iii) home exercise plus manual therapy delivered by a physical therapist. Ten treatment sessions will be performed in four weeks. During the trial, these patients will receive only the assigned treatment and the standard patient education and will be asked not to use any analgesics unless strictly necessary. Assessments by trained evaluators will occur at baseline, week 4 and week 12. The primary outcome measures will include visual analogue scale (VAS) for pain and neck disability index (NDI) at each time point. Secondary outcome measures will include cervical range of motion (CROM), pressure pain threshold (PPT), global perceived effect (GPE) and sick leave. Group by time differences will be analysed using linear mixed models with repeated measures.

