**Fig. 1 Fig1:**
[figure not shown]
Flowchart of research protocol

**Table 1 Tab1:** Inclusion and exclusion criteria

Inclusion criteria
**• **Age: 18 and 55 years • Office workers performing at least 4 h of computer work per day (on average) • Current neck pain, with or without pain in head or arm region • Experiencing pain for least 3 months, at a moderate or high pain intensity (≥ 5 of 10, Visual Analog Scale) • No cognitive impairment and volunteer to participate in the study
Exclusion criteria
• Pain caused by definite pathological factors, such as cerebrovascular diseases involving vertebral arteries, spinal cord pathology, cervical cancer or fracture • Neck pain secondary to diseases such as rheumatoid arthritis, ankylosing spondylitis and cervical spine infection • Suffering from cervical myelopathy or radiculopathy, coupled with motor, reflex, and/or sensory changes in the upper limb • Recurrent vertigo, or dizziness • Previous surgery to the cervical spine

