### Randomisation

After completing the baseline assessment, the eligible subjects will be randomised in equal portions to the home exercise group, Occiflex group and manual therapy group via a computer-generated block allocation with a block size of 6 or 9. Randomisation will be stratified by the baseline score (≤ 25 vs. ≥26 on a 0–50 scale) on the neck disability index (NDI) and balanced by gender in a 2: 1 ratio (female vs. male) for each group. This procedure ensures that the participants with the same severity of neck disability will be allocated to each group and that all groups are comparable in sex. Both the entry process and group allocation are unblinded to the researchers, examiners and participants.

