### Outcome measures

Personal information, including age, gender, BMI, international physical activity questionnaire (IPAQ) [24], working years and time since the onset of symptoms, will be collected at the baseline. The primary outcome measurements will include the VAS for pain and NDI to be administered at weeks 4 and 12. Secondary outcomes will include CROM, pressure pain threshold (PPT), global perceived effect (GPE) and sick leave. These evaluations will be carried out by an evaluator trained with these procedures. The adverse reactions during therapy will also be recorded.

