#### Visual analogue scale (VAS) for pain

The participants will be asked to indicate the intensity of their neck pain during the last week on a 10 cm horizonal scale, where 0 means no pain and 10 means unbearable pain [25]. The minimal clinically important change values range from 2.5 to 4.9 points for patients with neck pain, and an improvement below 1.5 points can be interpreted as irrelevant for pain intensity [26]. The VAS will be obtained at the baseline, week 4 and week 12 of the study period (post-treatment and 3 months follow up).

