#### Neck disability index (NDI)

The NDI is often used for a self-assessment of the cervical spine function of neck pain patients with validity and reliability [27]. This index consists of 10 questions covering different aspects of the patients’ daily life activities. Each item is rated on a scale of 0 to 5, where 0 means ‘no pain’ and 5 means ‘unbearable pain’. A higher score indicates greater disability. The clinically important difference for NDI is approximately 5 points to demonstrate treatment benefits after intervention [28]. The NDI will be measured at the baseline, week 4 and week 12 of the trial.

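### The group-by-time analysis of VAS and NDI names no baseline or randomisation covariate; read naturally it compares changes from baseline, which is unbiased but less precise than a baseline-adjusted contrast

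*Protocol article*

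**What the plan says.** The abstract of the protocol article sets the visits, "Assessments by trained evaluators will occur at baseline, week 4 and week 12", and the tested effect: "Group by time differences will be analysed using linear mixed models with repeated measures". The Statistical analysis section states that the outcomes "will be analysed by intention to treat and by using linear mixed models with repeated measures". It lists no fixed effects, covariates or covariance structure, and does not say how the baseline measurement enters.

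Both primary outcomes are collected at baseline. For VAS: "The VAS will be obtained at the baseline, week 4 and week 12 of the study period". For NDI: "The NDI will be measured at the baseline, week 4 and week 12 of the trial". The opening of Outcome measures is worded differently: "The primary outcome measurements will include the VAS for pain and NDI to be administered at weeks 4 and 12".

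The Randomisation section says "Randomisation will be stratified by the baseline score" of the NDI (25 or below against 26 or above) and balances the arms by gender. Neither factor is mentioned again in the analysis section.

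**The concern.** In a repeated-measures model with free arm means at all three visits, the group-by-time contrast at week 4 or week 12 is the arm difference at that visit minus the arm difference at baseline. Randomisation makes the expected baseline difference zero, so subtracting the observed one adds noise without removing bias. A model that uses baseline as a covariate, or that gives the arms a common baseline mean, estimates the same treatment effect with a smaller standard error.

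The other reading, weeks 4 and 12 only, has its own problem. Baseline is then unused, and a group-by-time test asks only whether the arm difference changes between the two visits. A benefit of equal size at both visits gives an interaction of zero.

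Precision on both primary outcomes is at stake, including the comparison of the two mobilisation methods.

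**Working it through.** **Inputs from the article (Sample size calculation).** NDI SD 8; difference 5 points; 150 participants in three equal arms; 20% dropout. Completers per arm: 150/3 × 0.8 = 40. Tests are two-sided at 0.05 (Statistical analysis).

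**Inputs assumed.** The correlation rho between baseline and follow-up, which the article does not give, is shown as a range. SDs are equal at all visits, with compound symmetry and complete data on the 40 per arm.

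**The plan's own figure.** The article states 38 per group for NDI, at 80% power and one-sided 5%. The usual formula gives 2 × [8 × (1.645 + 0.842)/5]² = 31.65, so 32; the two-sided version gives 40.19, so 41. Neither is 38. That is a separate matter: only the SD, the difference and the number of completers are used below. The sample size section uses no correlation.

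**Formulas.**
- Change contrast: SE = 8 × √(2(1 − rho)) × √(2/40)
- Baseline-adjusted contrast: SE = 8 × √(1 − rho²) × √(2/40)
- Variance ratio, adjusted to change: (1 − rho²)/(2(1 − rho)) = (1 + rho)/2
- Power = Φ(5/SE − 1.96)

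Example at rho 0.5: 8 × √1.0 × √0.05 = 1.79 against 8 × √0.75 × √0.05 = 1.55. Power is Φ(2.795 − 1.96) = 80% against Φ(3.227 − 1.96) = 90%.

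| rho (assumed) | SE, change | SE, adjusted | SE larger by | Power, change | Power, adjusted |
|---|---|---|---|---|---|
| 0.3 | 2.12 | 1.71 | 24% | 66% | 83% |
| 0.5 | 1.79 | 1.55 | 15% | 80% | 90% |
| 0.7 | 1.39 | 1.28 | 8.5% | 95% | 97% |
| 0.9 | 0.80 | 0.78 | 2.6% | >99% | >99% |

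**Check against the mixed model itself.** The generalised least squares information matrix for the three-visit model gives, at rho 0.3, 0.5 and 0.7, a week 12 group-by-time SE of 2.117, 1.789 and 1.386 with free baseline means. With a common baseline mean it gives 1.706, 1.549 and 1.277. The first set equals the change formula and the second the baseline-adjusted formula.

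**With Bonferroni.** If the planned correction covers three arm pairs (0.05/3 = 0.0167), NDI power at rho 0.3, 0.5 and 0.7 is 49, 66 and 89% for change against 70, 80 and 94% adjusted.

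**Weeks 4 and 12 only, baseline unused.** The arm difference at one visit has SE 8 × √(2/40) = 1.79 and power 80% whatever rho is. Since 2(1 − rho) exceeds 1 when rho is below 0.5, the change contrast is then worse than ignoring baseline altogether. The group-by-time term equals the week 12 difference minus the week 4 difference; for a constant benefit d it is d − d = 0.

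**VAS.** The table is not carried over to VAS. Entry requires a score of at least 5 (Table 1), so equal SDs at baseline and follow-up cannot be taken for granted.

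**The case against.** The strongest objection is that the article is silent on covariates and does not exclude them. It names a class of model, and a covariate list commonly sits in a full protocol or analysis plan, which is not shown. A reader might infer that the trial has decided to leave out baseline and the strata; the text does not support that, and the point is only that it names neither. A group-by-time model with a common baseline mean also fits the published words and is fully efficient. What remains is that the article does fix the tested effect, and the ordinary reading of that effect with three visits is the less efficient contrast.

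A reader might also infer that the VAS entry rule ("at a moderate or high pain intensity", at least 5 of 10) makes the loss worse by lowering the correlation. It does lower the correlation, but the inference is wrong in direction. The variance of change is the residual variance plus (1 − slope)² × the baseline variance. Cutting entry shrinks the baseline variance and leaves the slope and residual variance alone, so the change contrast moves closer to the adjusted one. In a simulation with assumed latent mean 5 or 6, SD 1.5 or 2 and entry restricted to 5–10, the adjusted-to-change variance ratio rises from 0.75 to about 0.86–0.90 at latent correlation 0.5, and from 0.85 to about 0.92–0.95 at 0.7.

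On the strata, no gain can be computed from the article. The NDI stratum is a dichotomy of baseline NDI and adds little to the NDI model once that score is included. No prognostic strength is given for gender.

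Finally, the loss is one of efficiency. The change contrast is valid, and at rho 0.7 it still has 95% power at 5% for NDI.

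**Conclusion.** The point holds as a free improvement in precision. On the natural reading, the NDI standard error is 24% larger than it need be at rho 0.3, 15% at 0.5, 8.5% at 0.7 and about 3% at 0.9. These figures rest on the article's SD of 8, 40 completers per arm, equal SDs, compound symmetry and an assumed correlation. Under those assumptions the change contrast is less precise at every rho below 1; only the size is uncertain. For VAS the same mechanism applies but the relative loss is likely to be smaller, and no size is claimed. No size is claimed for the strata either. On the weeks 4 and 12 reading, the problem is instead an interaction test that cannot detect a constant benefit. The article does not show that baseline or the strata have been excluded, and nothing here implies bias.

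**What to change.** In Statistical analysis, specify a mixed model on weeks 4 and 12 with arm, visit, arm-by-visit, baseline value of the outcome and baseline-by-visit. A constrained longitudinal model with all three visits and a common baseline mean is an equivalent choice. Add the NDI stratum and gender as fixed effects, and report the arm differences at week 4 and at week 12 as the results in place of the overall group-by-time test. Use the same model for CROM and PPT, which are also measured at baseline. Bring the abstract into line.

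The cost is wording only. Every variable is already collected, the planned software fits these models, and neither the sample size nor trial conduct changes. The text should be settled before outcome data are examined.

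### The primary mixed model gives way to an unnamed non-parametric test whenever Shapiro–Wilk rejects the residuals, so the trial's own data choose its primary method and estimand

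*Protocol article*

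**What the plan says.** Protocol article, Statistical analysis: VAS, NDI, CROM, PPT and GPE "will be analysed by intention to treat and by using linear mixed models with repeated measures". The abstract's Methods paragraph gives the contrast: "Group by time differences will be analysed using linear mixed models with repeated measures".

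The Statistical analysis section then adds a gate. "The Shapiro–Wilk test will be applied to test the normality", with no level of its own, and "In case of a non-normal distribution of the residuals, an appropriate non-parametric test will be conducted". No test is named. On multiplicity it says: "Multiple post-hoc comparisons will be conducted through Bonferroni’s contrast for parametric distributions". For missing data it offers two options, mean imputation or the mixed model itself.

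Sample size calculation plans for differences in means (5 NDI points with SD 8; 3 VAS points) and expects 20% dropout.

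Randomisation states that entry and allocation are not blinded for researchers, examiners or participants. It also says "Randomisation will be stratified by the baseline score" on the NDI, and that groups are "balanced by gender in a 2: 1 ratio (female vs. male) for each group". No section lists the fixed effects of the model.

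**The concern.** The gate is a rule that the article commits to, so it is more than a detail left out. It has three consequences.

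- **Method and estimand depend on the result of a test.** A reader cannot know in advance whether the primary result will be a difference in means at each visit or a rank statistic. On this text, nothing prevents the substitute being chosen by people who know the groups and have seen the data.
- **The fallback may not answer the planned question.** Kruskal–Wallis, Mann–Whitney and Friedman tests do not estimate a group-by-time mean difference. They also cannot use the mixed-model handling of missing values, which leaves mean imputation as the only other listed option.
- **Multiplicity is fixed on one branch only.** With three groups there are three pairwise comparisons, and the fallback branch has no stated rule for them.

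Shapiro–Wilk becomes more sensitive as residuals accumulate over visits, while inference on means becomes more robust. The gate can therefore discard a valid analysis because of a harmless departure.

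**Working it through.** **Inputs from the article.** 150 participants in three equal groups, so 50 per group; 20% dropout leaves 50 × 0.8 = 40 per group, or 120 in all. Two follow-up visits give 240 residuals and three visits give 360. NDI: difference 5, SD 8, scale 0–50. VAS: scale 0–10. Tests two-sided at 0.05.

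**The plan's own figure.** The article gives 38 per group for NDI at 80% power, one-sided. A two-sample t-test needs 33 one-sided or 42 two-sided at 80%; 38 corresponds to 85% power one-sided. That is a separate matter and does not decide this point. Only the difference of 5 and the SD of 8 are used below.

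**1. How often would the gate trigger?** Scores were drawn from a normal distribution, clipped at the scale limits and treated as independent, with Shapiro–Wilk at 5%. The means and the VAS SD of 2 (before clipping) are assumed. The planning VAS SD of 5 was not used: on a 0–10 scale it is the largest SD possible, with half the scores at each end.

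| Scores | Expected share at the floor | Rejected, n = 120 | Rejected, n = 360 |
|---|---|---|---|
| VAS mean 5, SD 2 | Φ(−2.5) = 0.6% | 2–3% | 8% |
| VAS mean 4, SD 2 | Φ(−2) = 2.3% | 8% | 61–62% |
| VAS mean 3, SD 2 | Φ(−1.5) = 6.7% | 79–81% | 100% |
| NDI mean 18, SD 8 | Φ(−2.25) = 1.2% | 4–5% | 14–16% |
| NDI mean 12, SD 8 | Φ(−1.5) = 6.7% | 78–82% | 100% |

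Ranges are from repeated simulations. Shape matters too: for a mildly skewed gamma distribution (skewness 0.5) the rejection rates are about 50%, 80% and 95% at n = 120, 240 and 360.

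**2. Would the departure have harmed the planned comparison of means?** A two-sample t-test with 40 per arm has a simulated type I error of about 5.0% on the gamma data. On clipped VAS scores with mean 3 it is 5.1–5.2%. The departures that trigger the gate here leave the test of means sound.

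**3. Multiplicity on the fallback branch.** For three groups and unadjusted two-sided 5% tests, the family-wise error is P(Q₃ > 1.96 × √2) = 12.2%, where Q₃ is the studentized range for three means. Simulated Mann–Whitney tests with 40 per arm give 11.7–12.5% with no overall test, and 4.8–5.3% when they follow a significant Kruskal–Wallis test.

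**4. What baseline adjustment would be worth, if baseline were ignored.** For a single-visit NDI comparison with 40 per arm, the noncentrality is 5 / (8 × √(2/40)) = 2.795 against a critical t of 1.991 on 78 df, so power is 78.8%. Adjusting for baseline with correlation ρ multiplies the SD by √(1 − ρ²):

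| Assumed ρ | Residual SD | Noncentrality | Power |
|---|---|---|---|
| 0.3 | 7.63 | 2.930 | 82% |
| 0.5 | 6.93 | 3.227 | 89% |
| 0.7 | 5.71 | 3.914 | 97% |

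**The case against.** The strongest reply is that this is a journal article, and the name of the fallback belongs in an analysis plan that is not shown. Rank-based methods for longitudinal factorial data also exist, so a non-parametric analysis need not lose the repeated visits. Both points are fair, and they limit what can be said about the fallback itself. They do not rescue the gate. Even a well-chosen, pre-named substitute would leave the primary method and its estimand to be settled by a significance test on the trial's residuals.

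Three stronger readings are tempting and are not supported.

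- **That the model omits the baseline value, NDI stratum and sex.** The article is silent on model terms, and silence is not exclusion. "The VAS will be obtained at the baseline, week 4 and week 12 of the study period", and NDI is measured on the same schedule, so in a group-by-time model baseline may already enter as the first time point. Covariate lists are commonly left to the analysis plan. If baseline NDI were ignored, the error would be conservative: power would be lost, with no excess of false positives.
- **That the fallback comparisons are uncorrected, with 12% family-wise error.** The text is silent here too. The comparisons are called post-hoc, which may imply a preceding overall test, and with three groups that brings the error back to about 5%.
- **That a switch is likely for both primary outcomes.** The table shows results from a few per cent to near certainty, depending on assumed means and shapes. It also uses independent scores, whereas the gate applies to model residuals.

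**Conclusion.** The concern holds for the gate. As written, a Shapiro–Wilk rejection replaces the primary mixed model with an unnamed test in an open-label trial. The usual candidates for that test would not deliver the mean differences promised in the abstract and used in the sample size calculation.

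The size is conditional. The chance of a switch is about 2% to 79% with 120 values and 8% to 100% with 360, for clipped VAS scores with assumed SD 2 and mean falling from 5 to 3. Family-wise error on the fallback branch is about 12% only if pairwise tests are both unadjusted and not preceded by an overall test. Neither figure is a prediction for this trial.

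On covariates there is no demonstrated error. The terms are unstated, and including them is advisable because NDI and sex enter the allocation. The power gain in step 4 applies only if baseline would otherwise be ignored, and it rests on assumed correlations.

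**What to change.** Rewrite the Statistical analysis section so that:

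1. One linear mixed model with group, visit and group-by-visit is the primary analysis for VAS and NDI, whatever the normality test shows. Mean differences between groups are reported at weeks 4 and 12.
2. Residuals are checked by plots, with robust or bootstrap confidence intervals if they look poor.
3. A named rank-based test is a sensitivity analysis only.
4. The same multiplicity correction applies to whichever test is used.
5. The model terms are stated and include the baseline value of the outcome, the NDI stratum and sex.

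The cost is wording and slightly more analysis work. No new data are needed: baseline VAS, baseline NDI and sex are already collected.

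### A Shapiro–Wilk test on the residuals decides whether the primary mixed model for VAS and NDI is replaced by an unnamed non-parametric test, which can change the contrast, its interval and the handling of missing visits

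*Protocol article*

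**What the plan says.** All of this is in the protocol article.

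- Abstract, Methods, defines the analysis: "Group by time differences will be analysed using linear mixed models with repeated measures".
- Statistical analysis says that the outcomes, with VAS and NDI as primary, "will be analysed by intention to treat and by using linear mixed models with repeated measures".
- The same section gives the reason for a pre-test, "The linear mixed model requires the residuals to be normally distributed", then the pre-test, "The Shapiro–Wilk test will be applied to test the normality", then the consequence, "In case of a non-normal distribution of the residuals, an appropriate non-parametric test will be conducted".
- The only significance level given is the general one: "All tests will be two sided, and the level of significance is set to 0.05".
- For missing data the section offers mean imputation or mixed modelling.
- Sample size calculation expects 20% dropout and uses clinically important differences of 5 NDI points and 3 VAS points.
- Table 1 admits participants with neck pain "at a moderate or high pain intensity (≥ 5 of 10, Visual Analog Scale").

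No other section softens the rule or limits the non-parametric test to a supporting role. The section does not say which residuals are tested (marginal or conditional), how large a departure matters, or which test follows.

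**The concern.** The form of the primary analysis hangs on a significance test of the trial's own residuals. The power of Shapiro–Wilk grows with the number of residuals, while inference on arm means becomes less sensitive to non-normality as the arms grow. The pre-test can therefore reject where the planned model is sound. Some non-normality is to be expected: VAS runs from 0 to 10 and is cut off at 5 at entry, and NDI is a sum of ten items scored 0 to 5, with a floor at 0.

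What is at stake is the content of the primary result:

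- Kruskal–Wallis or Mann–Whitney at each visit, or Friedman within an arm, does not test group by time.
- These tests yield no model-based difference in points with a confidence interval to compare with the protocol's own thresholds.
- They do not use partly observed participants as a mixed model does. If the mixed model goes, mean imputation is the only other stated way of handling missing data.
- If the residuals are tested outcome by outcome, VAS and NDI could be reported by different methods in one trial.

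**Working it through.** The protocol gives no figure for how the pre-test would behave, so there is none to reproduce. The check asks two things: how often the rule would fire, and whether the model is in trouble when it does.

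**Inputs from the protocol.** 150 participants in 3 equal arms, so 50 per arm. Visits at baseline, week 4 and week 12, so 150 × 3 = 450 residuals at most. Dropout of 20%, so 50 × 0.8 = 40 per arm, or 120 in all. The general level of 0.05 is assumed to apply to Shapiro–Wilk.

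**Assumed, because the protocol gives no distributions.** Each value is a participant effect plus a visit error, with no difference between arms.

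- Generic shapes: normal; gamma with shape 16, 4 or 2 (mean skewness of the conditional residuals about 0.3, 0.6 and 0.8); t with 8 df.
- VAS: means 6, 4, 4; participant SD 1.2 and error SD 1.5; clipped to 0–10; baseline at least 5. These SDs are smaller than the planning SD of 5.
- NDI: means 16, 10, 10; participant and error SD both 5; rounded and clipped to 0–50.

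**Formulas.** N participants, G = 3 arms, T = 3 visits.

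- Marginal residual: R_ij = Y_ij − mean of that arm at that visit.
- Conditional residual: R_ij − s·R̄_i, with s = max(0, 1 − MSE/MSB), MSE = Σ(R_ij − R̄_i)² / [(N−3)·2] and MSB = 3·ΣR̄_i² / (N−3).
- Group-by-time test under compound symmetry: F = (SS_interaction/4) / MSE, on (G−1)(T−1) = 4 and (N−3)·2 df. That is 234 error df for N = 120 and 294 for N = 150.

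**Results.** 3,000 simulated trials per row; each cell shows N = 120 / N = 150, in %.

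| Assumed shape | Pre-test rejects, conditional residuals | Pre-test rejects, marginal residuals | Type I error, group by time | Type I error, week-12 change |
|---|---|---|---|---|
| Normal | 3.9 / 4.7 | 7.8 / 6.7 | 5.5 / 6.0 | 5.1 / 5.3 |
| Gamma, shape 16 | 51.1 / 62.1 | 62.4 / 73.3 | 5.3 / 5.1 | 5.1 / 4.7 |
| Gamma, shape 4 | 97.5 / 99.4 | 99.5 / 99.9 | 5.1 / 5.1 | 4.3 / 4.3 |
| Gamma, shape 2 | 99.9 / 100 | 100 / 100 | 4.8 / 4.5 | 5.5 / 4.2 |
| t, 8 df | 40.2 / 46.5 | 40.3 / 45.7 | 5.1 / 5.2 | 5.6 / 5.1 |
| VAS as assumed | 8.7 / 9.6 | 22.7 / 29.8 | 5.3 / 4.6 | 4.7 / 4.3 |
| NDI as assumed | 20.9 / 24.5 | 73.5 / 87.3 | 5.6 / 6.1 | 4.9 / 5.5 |

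The Monte Carlo standard error of a 5% rate is √(0.05 × 0.95 / 3000) ≈ 0.4 percentage points. The highest type I error (6.1%, NDI) is hardly above the value for exactly normal data (6.0%), where the F test is exact.

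**Other assumptions, 150 participants and 3 visits.** With baseline VAS cut off at 5 (mean 6–7, SD 1.5–2, correlation 0.5), the pre-test on pooled residuals rejects in 6–68% of trials. With normal NDI floored at 0 it rejects in 19–76%. With gamma NDI (SD 8, means 10–20) it rejects in about 100%. At 40 per arm, ordinary model-based tests on such data hold 4.8–5.0% (VAS) and 4.6–4.8% (skewed NDI).

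**Reading.** Whether the rule fires says little about whether the model is valid. The unstated choice between conditional and marginal residuals alone moves the NDI rate from 24.5% to 87.3% at N = 150.

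**The case against.** The strongest reply has four parts.

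1. **The fallback is unnamed, so it may be a good one.** Rank tests on change from baseline, or rank-based factorial methods, could address all or part of the group-by-time question, and a full plan may name one. This stands. A reader might infer that the replacement cannot answer the trial's question, but that holds only for the usual rank tests, and the protocol does not commit to them.

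2. **The two-stage rule does no harm to type I error.** In a two-arm simulation (40 per arm, gamma data, SD 8, means 10, 15 and 20, correlation 0.5), baseline-adjusted ANCOVA was used unless Shapiro–Wilk rejected, and Mann–Whitney otherwise. Type I error was 5.3%, 5.0% and 5.2%; a repeat gave 4.8–5.9%. This stands, although it does not cover the full mixed model. The trigger is also stated in advance and depends on residual shape, not on which arm does better.

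3. **Ranks need not cost power.** For a 5-point shift in the same skewed data, the unadjusted t-test has 79/78/79% power against 92/84/80% for Mann–Whitney, and ANCOVA has 87/88/88% against 96/92/90% for rank ANCOVA. With normal NDI (difference 5, SD 8, 40 per arm, baseline correlation 0.3/0.5/0.7), ANCOVA gives 81/89/97% against 75–77% for unadjusted Mann–Whitney. The unadjusted t-test, however, gives only 78–79%, so most of that gap comes from the covariate. A reader might infer a general loss of power; like for like, the figures do not show it.

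4. **Arm means and SDs are reported in any case.** A raw difference can therefore be set against 3 or 5 points. This stands in part: what is lost is a model-based difference with its confidence interval.

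What none of this answers is that the primary contrast, its interval and the missing-data method can all change on a normality p-value.

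**Conclusion.** The point holds as a badly fixed decision rule. Detail that an article may leave to a fuller plan is a different matter: here the trigger and its consequence are both written into the protocol. The harm is a possible change in what is estimated, loss of an interval in scale points, and loss of likelihood-based use of partly observed participants when 20% of 150, or 30 people, are expected to drop out.

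The size of the risk cannot be pinned down. The 6% to nearly 100% range rests wholly on assumed distributions and on which residuals are tested. The entry cut-off and bounded scales make non-normality plausible, but a reader should not infer that the switch is near certain: for VAS the rate can lie close to the nominal 5%. The finding that the planned model keeps its level near 5% rests on the same assumed shapes and on complete visits.

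Severity: should be fixed before the data are seen. No invalid test has been shown, so it does not rank as a must-fix.

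**What to change.** In Statistical analysis, delete the Shapiro–Wilk step and the sentence that makes a non-parametric test the consequence. Replace them with text to this effect: the linear mixed model is the primary analysis of VAS and NDI whatever the distribution of the residuals; residual plots will be inspected; robust (sandwich) or participant-level bootstrap confidence intervals for the same contrasts will be reported as a sensitivity analysis. A rank-based analysis may be added if wanted, named in advance and labelled as sensitivity only.

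Cost: two sentences and one or two extra sensitivity runs, with no change to data collection or visits. One real downside is that some power may be forgone if the outcomes prove strongly skewed, as the skewed-NDI figures above indicate.

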### Sample size calculation

The sample size will be calculated using PASS 15.0.5 based on the means, standard deviations and an alpha of 5% (0.05) with a unilateral contrast. Assuming that the standard deviation of NDI scores is 8, then 38 participants per group will give the study 80% power to detect minimum clinically important differences (MCID) of 5 units in NDI [34]. Meanwhile, 41 participants per group are required based on the 10 cm VAS scale with a standard deviation of 5 and a clinically significant difference of 3 points [26]. To accommodate an expected dropout rate of 20% during follow-up and to have sufficient statistical power for the different variables in this study, a total of 150 participants will be sufficient.

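### Bonferroni for the three pairwise comparisons is valid but needlessly conservative; Holm gives the same family-wise guarantee with more power

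*Protocol article*

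**What the plan says.** The Statistical analysis section plans linear mixed models with repeated measures for the continuous outcomes, then states: "Multiple post-hoc comparisons will be conducted through Bonferroni’s contrast". The sentence limits this to the parametric case. The section adds: "All tests will be two sided, and the level of significance is set to 0.05". The Abstract describes the main analysis in one line: "Group by time differences will be analysed using linear mixed models with repeated measures". Nowhere does the article say that pairwise tests are run only after a significant overall test.

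The Randomisation section allocates equally to home exercise, Occiflex and manual therapy. The Objective names pairwise questions: Occiflex against manual therapy, and each of these against exercise alone. The Sample size calculation section supplies the NDI inputs: "Assuming that the standard deviation of NDI scores is 8, then 38 participants per group will give the study 80% power". The target there is a 5-point difference on the NDI, taken as the smallest that matters clinically.

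**The concern.** The trial's questions are pairwise, so the multiplicity rule sets the power of the answers. Bonferroni divides 5% by three for every comparison, whatever the other two show. With three arms that is more than error control requires. As soon as one pair of means truly differs, at most one of the three pairwise nulls can still be true. Holm and closed testing both use this kind of structure, and Bonferroni ignores it. At stake is the chance of confirming a real 5-point NDI difference with the participants already planned.

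**Working it through.** **Inputs.** NDI difference 5 and SD 8 (Sample size calculation). 150 randomised with 20% dropout: 150 × 0.8 / 3 = 40 completers per arm. Two-sided 5% (Statistical analysis). Assumptions: the family is the three pairwise comparisons at one outcome and visit; variance is pooled over three arms, df = 3 × 39 = 117; there is no gain from baseline adjustment or repeated measures.

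**The plan's own figure.** The stated 38 (NDI) and 41 (VAS) per group match a three-arm F test with one arm differing from two equal arms. The noncentrality is λ = n × (2/3) × (δ/σ)².
- NDI: 38 × (2/3) × (5/8)² = 9.90, power 79.98%.
- VAS: 41 × (2/3) × (3/5)² = 9.84, power 79.83%.

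Two-group formulas do not reproduce them: for NDI they give 32 to 33 per group one-sided and 41 to 42 two-sided.

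**Bonferroni power.** The standard error of a pairwise difference is 8 × √(2/40) = 1.789, so the noncentrality is 5/1.789 = 2.795. The two-sided critical value on 117 df is 1.980 at 5% and 2.429 at 1.67%. The noncentral t gives 79.2% unadjusted and 64.3% with Bonferroni.

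**Alternatives.**
- Holm: order the three p-values and compare the smallest with 0.05/3, the next with 0.05/2 and the last with 0.05, stopping at the first failure. Its first step is Bonferroni and later steps are easier, so it never rejects less.
- Closed test: three-arm F test at 5%; if significant, each pairwise test at 5%.

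Simulated power for a 5-point contrast at 40 per arm (200,000 trials per pattern, simulation standard error about 0.1 point):

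| True means: home exercise, manual, Occiflex | Bonferroni | Gate, then Bonferroni | Holm | Closed |
|---|---|---|---|---|
| 0, 0, 5 | 64.3% | 64.1% | 67.7% | 74.6% |
| 0, 2.5, 5 | 64.6% | 64.1% | 65.4% | 68.5% |
| 0, 3, 8 | 64.2% | 64.2% | 73.2% | 79.0% |
| 0, 5, 10 | 64.2% | 64.2% | 77.5% | 79.2% |

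The contrast is Occiflex v manual in rows 1, 3 and 4, and Occiflex v home exercise in row 2. The last row is an extreme case: it needs a 10-point gap between the outer arms, twice what the plan assumes.

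With no dropout (50 per arm) and means 0, 0, 5, the figures are Bonferroni 75.9%, Holm 79.0% and closed 84.6%.

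**Family-wise error at 40 per arm.**
- All three arms equal: Bonferroni 4.3%, Holm 4.3%, closed 5.0%, unadjusted about 12%.
- One true null (0, 0, 5): Bonferroni 1.7%, Holm 3.2%, closed 4.9%.

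**Limit on the closed test.** The gate must concern the same visit. If the arms differ at week 4 only, an overall group-by-time test can be significant while all three week-12 nulls are true. Three unadjusted week-12 tests would then carry about 12% family-wise error.

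**The case against.** **It is a choice between valid methods.** Bonferroni controls the family-wise error, needs no gate and gives simple simultaneous intervals. Nothing in the Statistical analysis section is wrong or contradictory on this point, and an analysis plan that is not shown may refine the procedure. All of this stands and limits the point to an efficiency suggestion. It does not remove the suggestion, because Holm also needs no gate and is never less powerful.

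**A double correction?** A reader might infer from the term post-hoc, and from sample sizes that match a three-arm F test, that Bonferroni is stacked on an omnibus test and that the power loss comes from correcting twice. The documents do not support this. No gate is stated. If one were used, it would cost at most about 0.5 point (second and third columns of the table), and family-wise error with all arms equal would move only from 4.3% to 4.2%. The loss is that of Bonferroni itself.

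**A general 10 to 15 points?** That gain appears only against the closed test in some patterns. With the third arm midway the closed test gains about 4 points and Holm about 1; with one arm different from two equal arms, Holm gains about 3. The comparison with unadjusted tests (79.2% v 64.3%) is not a fair yardstick, since those have about 12% family-wise error.

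**Conclusion.** The point holds as a cheap improvement. Bonferroni is valid but wastes some power with three arms. At 40 completers per arm, a true 5-point NDI contrast has about 64% power under Bonferroni. In the first three patterns Holm raises this by about 1 to 9 points, to 65 to 73%, and a per-visit closed test by about 4 to 15 points, to 68 to 79%. Both hold family-wise error at 5% per outcome and visit. The size depends on where the third arm lies, which the plan does not state, and on the assumptions listed with the inputs; baseline adjustment or repeated measures could raise every figure.

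Two matters lie outside this point. Control across two primary outcomes and two visits is separate, and neither Holm nor the closed test as set out here supplies it. So is the mismatch between a sample size described as "an alpha of 5% (0.05) with a unilateral contrast" and a two-sided, Bonferroni-adjusted analysis.

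**What to change.** Replace the Bonferroni sentence with one to this effect: for each outcome and visit, the three pairwise group differences will be tested two-sided with Holm-adjusted p-values at a family-wise level of 5%. Holm needs only the three unadjusted p-values, so the model does not change.

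If a closed test is preferred, state that at each visit a three-arm test at 5% comes first and that pairwise tests at 5% follow only if that visit's test is significant. State also that the overall group-by-time test does not serve as the gate.

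The cost is one sentence and no extra participants. The downside is in the intervals: unadjusted pairwise 95% intervals are not simultaneous and may not match the adjusted p-values, so they should be labelled as unadjusted. Bonferroni intervals can be shown beside them.
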